**Fig. 2 Fig2:**
[figure not shown]
Schedule of enrolment, interventions, and assessments. ^1^ Phone visit; (X) will be performed in case it has not been done within the period of 3 weeks prior to the start of the medication

### Plans to promote participant retention and complete follow-up {18b}

Patients will be contacted every 3 months, either in person with a medical visit or by phone call, in order to maintain a close contact with the patient as to ensure treatment compliance and reduce the risk of loss to follow-up.

### Data management {19}

The study will collect three types of data:Clinical data: will consist of numerical data that will be obtained by the staff during the clinical visit or after blood tests (that will be downloaded from the clinical history as a .pdf file)Imaging data: will consist of images (.tiff or .psd files) that will be obtained by MRI and X-ray and that will be analyzed with the corresponding program software.Information from patient questionnaires (Kidmed nutrition questionnaire)

Patient data will be recorded in anonymized form (without reference to the patient’s name) using exclusively the patient's identification code. Patient identification code lists will remain at the recruiting sites and will be stored separately from the trial data. These data will be only used for the re-identification of the patients, if needed.

The research data of this project will be stored in a REDCap database. The data will be collected and entered in the electronic database by the members of the research group (using a username and password). The consistency and quality of the data will be controlled to ensure that no data are accidentally changed and the accuracy of data is maintained over its entire life cycle.

At the end of the project, data will be recovered from REDCap and an SPSS file (.sav) will be created to perform the statistical analysis of the results. No sensitive data will be present in this file.

### Confidentiality {27}

All data of this trial will be anonymized and recorded on the hospital’s servers. No sensitive data will be externally available.

### Plans for collection, laboratory evaluation, and storage of biological specimens for genetic or molecular analysis in this trial/future use {33}

Blood samples will be processed and stored (at −80 °C) at the Pediatric Endocrinology lab (IDIBGI) and at the Metabolic Endocrinology lab (IRSJD) until analysis. The remnant samples will be kept in a private collection with registration code C0007072 (Instituto de Salud Carlos III; Madrid) to be used in future studies related to this research line.

## Statistical methods

### Statistical methods for primary and secondary outcomes {20a}

The statistical analyses will be performed with the SPSS program, version 23.0 (SPSS, Chicago, Illinois, USA). The analysis of quantitative variables of independent groups will be performed using ANOVA for repeated measurements in models adjusted for potential confounding variables. The association between BA, clinical variables, endocrine-metabolic, and imaging variables will be sought by correlation and multiple regression analysis. A statistical analysis will be done by intention to treat and another with the patients who have completed follow-up. *p*<0.05 will be considered statistically significant.

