### Outcomes {12}

#### Primary outcome

The primary outcome is annualized bone age (BA) advancement over the on-treatment year. A hand and wrist X-ray of the left hand will be obtained at the treatment start and after 1 year on treatment. BA advancement will be measured by an automated/blinded method called BoneXpert (Visiana, Denmark) [1].

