#### Assessment of outcomes

*Bone age:* A hand and wrist X-ray of the left hand will be taken at the Radiology Department either at HJT or HSJD, at treatment start and after 1 year on treatment. At each center, bone age will be determined with the same BoneXpert programme [version 3; February 2021 (Visiana, Denmark)] [38]. This method will yield bone ages by Greulich & Pyle (GP) and by Tanner-Whitehouse 2 (TW2). Bone age maturation will be annualized by calculating the ratio between the increase of BA over the increase in CA (ΔBA/ ΔCA) [38].

*Clinical characterization:* Clinical variables will be obtained during the clinical visits with the pediatric endocrinologist at HJT and HSJD. The same investigator at each center will assess the clinical variables at times 0, 6 months, 1 year, and 2 years. Halfway the second post-treatment year, the girls will be contacted by phone to discuss the absence or timing of menarche.

*Blood sampling:* 23 mL of peripheral blood in a fasting state will be drawn in the early morning at each clinical center, at baseline (time 0), after 6 months on treatment, after 1 year on treatment, and 1 year off treatment. Blood samples will be stored (at −80 °C) at the Pediatric Endocrinology lab (IDIBGI) and at the Metabolic Endocrinology lab (IRSJD) until analyses.

*Endocrine-metabolic variables analysis:*

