The clinical laboratory at both HJT and HSJD will be responsible for analyzing (1) glucose (by the glucose oxidase method); (2) fasting insulin, IGF-I, SHBG, and usCRP (by immuno-chemiluminescence); (3) LH, FSH, and oestradiol (by immuno-chemiluminescence); (4) total cholesterol, LDL-cholesterol, HDL-cholesterol, and triglycerides (by molecular absorption spectrometry).Circulating testosterone and androstenedione concentrations will be centrally assessed at the Bioanalysis Research lab [Institut Hospital del Mar d'Investigacions Mèdiques (IMIM), Hospital del Mar] by liquid chromatography-tandem mass spectrometry. The free androgen index (FAI) will be calculated with the following formula: testosterone (nmol/L) × 100/SHBG (nmol/L).The analysis of circulating HMW-adip, GDF-15, and CXCL14 concentrations will be centralized at the Metabolic Endocrinology laboratory (IRSJD). Circulating levels of HMW-adip will be analyzed by ELISA (Millipore, St Louis, MO), with intra- and inter-assay coefficients of variation (CVs) <9%. Serum GDF-15 will be assessed using a specific human ELISA kit (R&D Systems, Minneapolis) with intra- and inter-assay CVs <6%. Serum CXCL14 will be assessed using a specific ELISA kit (Ray Biotech, Norcross, GA, USA), with a sensitivity of 0.7 ng/ ml, and inter- and intra- assay CV less than 12%.

*Safety markers analysis:* The clinical laboratories at HJT and HSJD will analyze (1) blood count (by flow cytometry and colorimetric assay); (2) circulating levels of ALT, AST, GGT, TSH, urea, electrolyte panel, and creatinine (by molecular absorption spectrometry); and (3) vitamin B12 and folic acid (by immuno-chemiluminescence).

*Abdominal and hepatic fat assessment:* Abdominal fat distribution *(subcutaneous and visceral)* and intrahepatic fat will be analyzed by MRI at both clinical sites with the same scan [multiple slice 1.5 Tesla scan (Signa LX Echo Speed Plus Excite, General Electric Healthcare, Milwaukee, WI)]. The assessments will be performed at Clínica Girona (Girona) and CETIR Medical Centre (Barcelona). Scans will be performed by the same operator at each center, blinded to the treatment allocation, at times 0, 6 months, 1 year, and 2 years. A central reader blinded to treatment allocation will be appointed to process and interpret the images from both study centers (QUIBIM, Valencia, Spain).

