### Methods in analysis to handle protocol non-adherence and any statistical methods to handle missing data {20c}

An intention-to-treat analysis will be performed including all participants randomized to either placebo or mini-spiomet, ignoring non-compliance, protocol deviations, withdrawal, and anything that happened after randomization. If necessary, for the withdrawn participants, the missing data will be filled with the data of previous visits.

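### For the multi-visit secondary outcomes, repeated-measures ANOVA in its usual form drops a girl who stays in the trial but misses one measurement, and the plan's only filling rule does not cover her

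*Protocol article*

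**What the plan says.** All references are to the protocol article.

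- **Method.** Section {20a} says the analysis of quantitative variables "will be performed using ANOVA for repeated measurements in models adjusted for potential confounding variables". On software it says: "The statistical analyses will be performed with the SPSS program, version 23.0". The SPSS procedure and the visits that enter a model are not named.
- **Analysis sets.** Section {20a}: "A statistical analysis will be done by intention to treat and another with the patients who have completed follow-up". Section {20c}: "An intention-to-treat analysis will be performed including all participants randomized to either placebo or mini-spiomet", whatever happens to them after randomisation.
- **Missing data.** Section {20c} gives one rule: "If necessary, for the withdrawn participants, the missing data will be filled with the data of previous visits".
- **Visits.** Under Assessment of outcomes in {18a}, blood is drawn "at baseline (time 0), after 6 months on treatment, after 1 year on treatment, and 1 year off treatment", and MRI is done by an operator "blinded to the treatment allocation, at times 0, 6 months, 1 year, and 2 years". Clinical variables follow the same four visits.
- **Primary outcome.** Section {12}: "A hand and wrist X-ray of the left hand will be obtained at the treatment start and after 1 year on treatment". These two films give one bone-age to chronological-age ratio per girl.

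**The concern.** Classical repeated-measures ANOVA needs a value at every modelled visit. A girl with one gap loses her whole row, including the visits at which she was measured. The filling rule in {20c} is limited to girls who withdraw, so it does not help a girl who remains in follow-up but misses an MRI or whose sample is lost. For her, the named method does not deliver the all-randomised analysis that {20c} promises.

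Withdrawn girls do stay in, but only through earlier values entered as if they had been measured. Eligibility requires progressive puberty, so these values are expected to move. A girl who leaves before month 6 would be entered with no change from baseline. A girl who leaves after month 12 would have her on-treatment value standing in for the off-treatment visit.

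The affected outcomes carry weight. Reduction of hepatic and visceral fat is the first specific objective in section {7}, and persistence one year after stopping is the third. At stake are precision that has already been paid for and, if gaps relate to response or tolerability, some bias.

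**Working it through.** **1. The plan's own figure.** Section {14} gives 21 girls per arm from a difference of 0.20, SD 0.2 and 90% power. With two-sided alpha 0.05 (the article prints 0.05%, but only 0.05 reproduces the number): 2 × (1.960 + 1.282)² × (0.2/0.2)² = 21.01 per arm. Allowing for one-third loss, 21/(1 − 1/3) = 31.5, so 32 per arm and 64 in total. This calculation is for the bone-age ratio, which needs only the films at 0 and 12 months, so the present point does not change it.

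**2. Who is kept under the plan as written (intention-to-treat analysis, multi-visit variable)**

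| Girl | Rule in {20c} | Result in a complete-row ANOVA |
|---|---|---|
| All modelled visits measured | none needed | kept |
| Withdrawn | filled from earlier visits | kept, with filled values treated as measured |
| Still in the trial, one measurement missing | none | deleted at all modelled visits |

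The third row conflicts with the promise to analyse everyone randomised.

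**3. Possible size.** The documents give no rate of missed measurements, so the rate p is an assumption. It applies per follow-up visit, independently, to girls who have not withdrawn, with baseline present for all. With k follow-up visits in the model:

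- share deleted = 1 − (1 − p)^k
- month-12 standard error relative to using every girl with a month-12 value = √[(1 − p)/(1 − p)^k]

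| p (assumed) | Deleted, months 6, 12, 24 (k = 3) | SE ratio | Deleted, months 6, 12 (k = 2) | SE ratio |
|---|---|---|---|---|
| 3% | 1 − 0.97³ = 8.7% | 1/0.97 = 1.03 | 1 − 0.97² = 5.9% | 1/√0.97 = 1.02 |
| 5% | 1 − 0.95³ = 14.3% | 1/0.95 = 1.05 | 1 − 0.95² = 9.8% | 1/√0.95 = 1.03 |
| 10% | 1 − 0.90³ = 27.1% | 1/0.90 = 1.11 | 1 − 0.90² = 19.0% | 1/√0.90 = 1.05 |

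In girls, if nobody withdraws and k = 3: at 5%, 64 × 0.95³ = 54.9 complete rows against 64 × 0.95 = 60.8 with a month-12 value; at 10%, 46.7 against 57.6. If a third withdraw, the percentages apply to the remaining 64 × 2/3 ≈ 43, so about 6 (5%) or 12 (10%) of those are deleted.

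**4. Does month-12 inclusion depend on the 2-year visit?** Only if both visits share a model. Section {21b} places analysis after the end of the trial, and {19} describes one SPSS file created then. Section {17a} locks the on-treatment data separately so that they can be analysed. These statements do not settle the question. Under k = 2 a missed month-6 visit still removes a girl who has month-12 data.

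**The case against.** The strongest reply is that an article need not name the SPSS procedure, the visits or the covariates, and that the named software also offers a mixed-model procedure that does not delete rows. This stands in part: listwise deletion is the ordinary reading of the stated method, not a certainty. That reading is supported by the filling rule, which a likelihood-based mixed model would not need.

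Second, {20c} does keep withdrawn girls in, and contact every three months is planned to limit loss. The gap is therefore confined to girls who remain in follow-up with a missing measurement, and how many there will be is unknown.

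Three stronger readings are tempting but unsupported:

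- **Missing the 2-year visit removes a girl from the month-12 comparison.** No section says the two visits share a model, and the separate on-treatment lock in {17a} leaves the opposite open.
- **The planned one-third loss shrinks the analysis.** A reader might spread that loss evenly over 24 months and infer 64 × 5/6 ≈ 53 girls with month-12 data but only 64 × 2/3 ≈ 43 complete rows. Those losses are withdrawals, which {20c} fills in the intention-to-treat analysis; the same girl cannot be both filled and deleted.
- **The primary outcome is affected.** It is one ratio per girl from two films, with no month-6 or 2-year value.

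**Conclusion.** The point holds for the multi-visit secondary outcomes only. The stated ANOVA, in its usual complete-row form, and a filling rule limited to withdrawn girls together leave out a girl who stays in the trial with one gap, contrary to the promised analysis of all randomised girls. Withdrawn girls are retained only by treating carried-forward values as data in a population expected to change.

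The size depends on assumed independent miss rates among girls who have not withdrawn. At 5% or 10% per follow-up visit, about 14% or 27% of them are deleted if months 6, 12 and 24 are modelled together, with a month-12 standard error about 5% or 11% larger. The deletion is about 10% or 19% in a 0/6/12-month model. Dependence of month-12 inclusion on later attendance is conditional on a joint model, which the article leaves open. This is a moderate loss of precision with possible bias in secondary results. It is worth correcting, and the primary analysis is not under threat from it.

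**What to change.** For secondary outcomes measured at several visits, replace repeated-measures ANOVA with carry-forward by a linear mixed model for repeated measures (SPSS MIXED):

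- response: all observed follow-up visits, with the modelled visits named;
- fixed effects: arm, visit, arm-by-visit interaction, and the baseline value as covariate;
- unstructured covariance across visits;
- month 12 (on treatment) and month 24 (post-treatment) read as contrasts from the model;
- carry-forward kept, if wanted, as a sensitivity analysis.

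This keeps month-6 and month-12 values already collected under either reading of which visits are modelled together. The cost is a sentence or two of analysis text and slightly more analysis work, with no extra data or new software. The method relies on missing at random, which should be stated. A girl with no follow-up value for a variable still contributes nothing to its contrasts, and the text should say so.

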### Interim analyses {21b}

No interim analysis will be done. Statistical analysis will be done once the trial has been finished.

### Methods for additional analyses (e.g., subgroup analyses) {20b}

No subgroup analysis will be done.

### Methods in analysis to handle protocol non-adherence and any statistical methods to handle missing data {20c}

An intention-to-treat analysis will be performed including all participants randomized to either placebo or mini-spiomet, ignoring non-compliance, protocol deviations, withdrawal, and anything that happened after randomization. If necessary, for the withdrawn participants, the missing data will be filled with the data of previous visits.

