### Sample size {14}

In a previous study performed in girls with a history of low-BW and rapid postnatal catch-up in weight, metformin treatment for 4 years (425 mg for 2 years, then 850 mg for 2 years) slowed down the accelerated bone maturation [38]. The progression of bone maturation, as assessed by the mean ratio of Δ BA over Δ CA, was faster in untreated girls [≈1.20 ± 0.2 (SD)] as compared to metformin-treated girls [≈1.00 ± 0.2 (SD)] (*P*≤0.05). To obtain a significance level of 0.05% and power of 90%, a total of 42 girls (21 in each study arm) must be included to detect the minimal relevant difference in bone age progression (1.20 vs 1.00 years) (https://clincalc.com/stats/samplesize.aspx). The number of patients has been further increased (*n*=32 in each study arm) to guarantee the necessary sample size, in the case up to one third of the participants drop out of the study.

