### Procedure for unblinding if needed {17b}

If a girl/family wishes to withdraw from the trial or if an adverse event leads to withdrawal from the study, then the family will be invited to an end-of-study visit which will be followed by disclosure of treatment allocation. The girl will continue to receive standard care.

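### Carry-forward can score a girl who leaves before the 1-year X-ray as having no bone-age advancement, so withdrawals can dilute, create or erase the primary effect

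*Protocol article*

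**What the plan says.** Four statements in the protocol article have to be read together.

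- **Missing data (section {20c}).** "An intention-to-treat analysis will be performed including all participants randomized to either placebo or mini-spiomet", whatever happens after randomization. Then: "If necessary, for the withdrawn participants, the missing data will be filled with the data of previous visits". No criterion says when filling is needed, and no outcome is exempted.
- **Primary outcome (Outcomes {12}).** "The primary outcome is annualized bone age (BA) advancement over the on-treatment year". The same section fixes when the films are made, at two time points only: "A hand and wrist X-ray of the left hand will be obtained at the treatment start and after 1 year on treatment". The collection schedule in {18a} agrees: the 6-month visit has clinical, MRI and blood assessments, and the follow-up X-ray is listed only after 1 year.
- **Formula (Assessment of outcomes, {18a}).** "Bone age maturation will be annualized by calculating the ratio between the increase of BA over the increase in CA".
- **Expected loss (Sample size {14}).** The number per arm was raised from 21 to 32 to protect the trial "in the case up to one third of the participants drop out of the study".

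Two further statements bear on the point. On withdrawal, "the family will be invited to an end-of-study visit which will be followed by disclosure of treatment allocation" (section {17b}); the text does not say what is measured at that visit. And section {20a} plans two analyses without ranking them: "A statistical analysis will be done by intention to treat and another with the patients who have completed follow-up".

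**The concern.** Carry-forward needs an earlier on-treatment value to carry. The primary outcome has none: before 1 year the only bone age is the baseline one. Filling it in makes the bone-age change zero. That is not a cautious guess. A growing girl does not stand still for a year, and because less advancement is the desired result, zero counts as an extreme success. A girl who leaves because she tolerates the tablet badly would improve her arm's mean.

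The same rule freezes other variables that move with puberty, such as height, Tanner stage, LH, oestradiol and IGF-I, at the last visit attended.

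The rule also clashes with the sample-size reasoning. Section {14} treats girls who drop out as lost and aims to keep about 21 per arm with data. Section {20c} puts them back with filled values. At stake is whether the intention-to-treat result reflects bone maturation or the pattern of withdrawals.

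**Working it through.** **Inputs.** From section {14}: means 1.20 (untreated) and 1.00 (treated), SD 0.2 in each, power 90%, 32 per arm, loss up to one third. Section {20a} sets significance at p<0.05; two-sided testing is my assumption. Section {14} prints the level as 0.05%, but only 5% reproduces its sample size; a literal 0.0005 would need 46 per arm. Loss rates by arm are not in the protocol and are assumed below.

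**Step 1. The plan's own figure.** n per arm = 2 × (1.960 + 1.282)² × 0.2² / 0.20² = 21.01, against 21 stated. Allowing for one-third loss: 21 / (1 − 1/3) = 31.5, so 32. Both agree with the protocol. Analysing only observed 1-year values at one-third loss leaves about 21 per arm, a difference of 0.20 and power of about 90%, provided loss is unrelated to maturation.

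**Step 2. Value given to a girl without a second film.** BA at 1 year := BA at baseline, so ΔBA = 0. With her true age at 1 year, the ratio is 0 / 1 = 0. If age is carried forward as well, it is 0/0 and undefined. On the zero reading she lies 1.20/0.2 = 6 SD below the untreated mean and 1.00/0.2 = 5 SD below the treated mean.

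**Step 3. Arm mean and variance with a fraction d scored 0.**
- mean = (1 − d)μ
- variance = (1 − d) × 0.2² + d(1 − d)μ²

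At d = 1/3:
- placebo: mean 0.80; variance 0.027 + 0.320 = 0.347; SD 0.59
- mini-spiomet: mean 0.667; variance 0.027 + 0.222 = 0.249; SD 0.50
- difference 0.133; standard error √[(0.347 + 0.249)/32] = 0.136; ratio 0.98
- power ≈ Φ(0.98 − 1.96) ≈ 16%

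A simulation of 40,000 trials (two-sample t-test, loss independent of outcome) also gives 16%.

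**Step 4. Equal loss in both arms, 32 per arm, true effect 0.20.**

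| Loss in each arm | Expected difference | Power |
|---|---|---|
| 0% | 0.20 | 98% |
| 5% | 0.19 | 68% |
| 10% | 0.18 | 47% |
| 20% | 0.16 | 27% |
| 33.3% | 0.13 | 16% |

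With no true effect and one-third loss in both arms, the simulated two-sided rejection rate stays about 5%.

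**Step 5. Unequal loss, no true effect (both means 1.20).** The spurious difference is 1.20 × (loss on mini-spiomet − loss on placebo).

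| Mini-spiomet vs placebo loss (assumed) | Spurious difference | False benefit (nominal 2.5%) |
|---|---|---|
| 20% vs 10% | 0.12 | 17% |
| 33.3% vs 16.7% | 0.20 | 31% |
| 30% vs 10% | 0.24 | 47% |

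A gap of 16.7 percentage points, about 5 girls in 32, gives the whole planned effect. These rates average over the chance number of withdrawals. For fixed counts five apart, the false-benefit rate depends on the total lost: 53% at 5 vs 0 and 4% at 10 vs 5, because more zeros also widen the SD.

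**Step 6. Unequal loss the other way, true effect 0.20.** With 8 placebo and 3 mini-spiomet withdrawals, the means are 24/32 × 1.20 = 0.900 and 29/32 × 1.00 = 0.906. The effect is gone.

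**The case against.** A reader might infer that every girl who withdraws is scored zero, and that the intention-to-treat result is therefore driven by drop-out rather than by mini-spiomet. The documents do not support that, for these reasons:

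- The primary outcome covers only the on-treatment year. Girls who leave in the off-treatment year already have both X-rays.
- The rule is conditional and limited to girls who withdraw. Section {11b} gives reasons for stopping medication, not for leaving the trial, and the intention-to-treat set keeps girls who do not comply. The step from side effects to a missing X-ray is an inference.
- The end-of-study visit might supply a film, and a ratio over actual age could use it. The text lists none, and the schedule figure is not shown, so this cannot be settled.
- If age is carried forward too, the outcome is undefined. The rule is then unworkable for this endpoint, but it creates no spurious benefit.
- With equal loss, the direction is kept and type I error is not inflated. Creating or erasing an effect needs unequal loss. The protocol gives only an overall ceiling, and its background section describes the components as well tolerated.
- A completers analysis is planned and does not rest on the filled values.

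These points limit the scope and certainty of the concern. They do not rescue the rule. For a girl with no second film, neither reading gives a usable value. The completers analysis has its own selection problem and, since neither analysis is named primary, it does not settle which result counts if the two disagree.

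**Conclusion.** The point holds in limited form. For a girl who leaves before the 1-year X-ray and has no other film, the stated rule yields either 0, better than the treatment target of 1.00, or an undefined ratio.

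On the zero reading and the protocol's planning values, the damage under equal loss is dilution: 10% loss per arm already roughly halves power, and the one-third allowance takes it to about 16%. Under unequal loss the bias can go either way. About five extra withdrawals on mini-spiomet match the planned effect on average, and a similar excess on placebo cancels a real one.

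The calculations assume loss unrelated to bone maturation and an unadjusted two-sample comparison in place of the planned adjusted ANOVA. The unequal rates are illustrations, not forecasts. If few girls leave in the first year, the effect is smaller.

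**What to change.** 1. Delete carry-forward for bone age and for other variables that change with puberty.
2. State that the already planned 1-year X-ray is sought from every randomized girl still willing to attend, whether or not she stopped the tablets. Use any film taken at another interval through its actual ΔBA/ΔCA.
3. For values still missing, use a likelihood-based analysis or multiple imputation with few predictors, for example arm, centre, baseline bone age and age. With 64 girls and possibly one third missing, a long predictor list would be fragile, and 6-month predictors are absent for girls who leave earlier. Add a placebo-based imputation as the sensitivity analysis.
4. Use a mixed model for the repeated secondary outcomes.
5. Name the intention-to-treat analysis as primary and the completers analysis as supportive.

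The cost is protocol and analysis-plan wording and a little more programming, with no extra patients and no new procedure. The small downside is that confidence intervals will show the information that is really missing.
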